### Randomization and masking

Eligible, consented patients will be randomly assigned in a 1:1 ratio to receive either dexamethasone plus standard intensive care or standard intensive care alone (control group). Dexamethasone will be freely provided by the health authorities in participating hospitals. Because of the emergency nature of the trial, a placebo will not be used. According to the ethical principles for medical research of the Declaration of Helsinki [12], the use of no placebo (no intervention) is acceptable when no proven intervention exists. The Spanish Agency of Drugs and Medical Devices and the Ethics Committees did not mandate a blinded design or the administration of a placebo. Central randomization will be done within the REDCap system. Local investigators in participating ICUs are the only authorized personnel to interact with the web-response system through a username and password. Once eligibility is confirmed in the eCRF, the next available treatment group is assigned by the system according to a randomization schedule prepared by a statistician and uploaded as a look-up table to the REDCap system. The computer-generated randomization schedule will use random permuted blocks of varying sizes to further ensure allocation concealment and is unavailable to those who enroll patients or assign interventions.

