### Dexamethasone therapy and general procedures

Patients assigned to the dexamethasone group will receive the first dose immediately after being randomized. Patients in the dexamethasone group will receive an intravenous dose of 20 mg once daily from day 1 to day 5, and 10 mg once daily from day 6 to day 10. We selected the same doses as reported in the only published trial with dexamethasone in ARDS patients [8]. Treatment with dexamethasone will be given for a maximum of 10 days after randomization, independently of the intubation status (Fig. 1). Criteria for discontinuing intervention (exiting the trial) for a given trial participant are contemplated in the informed consent from (at patient’s legal representative request). In addition, as a request by the patient’s legal representative, allocated intervention (daily dose of intravenous dexamethasone) could be modified in case of a profound worsening of disease status (request to do-not-resuscitate orders, withdrawal of treatment and life support measures).

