### Clinical and laboratory monitoring

All participating patients, regardless of the study arm into which they are randomized, will be monitored and managed following general standard of care practices. Patients will be assessed once daily by trained physicians and nurses using a simplified standardized case report form (CRF) that captures data on lung mechanics, gas-exchange, and routine biochemistry and hematological test on days 0 (at ARDS diagnosis), 1, 3, 6, and 10, and every 10 days, including the last day of MV, if the patient is still in the ICU (Fig. 2). The model of CRF can be obtained from the primary investigator. Recommended lab determinations include creatine phosphokinase (CPK), D-dimer, ferritin, lactate dehydrogenase (LDH), troponin, lactate, creatinine, procalcitonin, C-reactive protein (CRP), lymphocyte count, and interleukin-6 (IL-6). Viral serology (antibodies) and routine blood cultures will be indicated at the discretion of the attending physician. We will record complications, such as other infections, barotrauma, and sepsis; Acute Physiology and Chronic Health Evaluation II (APACHE II) score [18] on days 0 and 1; and the Sequential Organ Failure Assessment (SOFA) score [19], on days 0, 1, 3, 6, and the last day of MV, if the patient is still in the ICU. Serial oropharyngeal swab samples will be obtained on day 1 (before the administration of the first dose of dexamethasone) and (if possible) on days 6, 10, 14, 21, and 28 until discharge or death occurs, and tested at participating hospitals using real-time RT-PCR. RNA will be extracted using standard measures by trained personnel from the Microbiology Departments in each hospital. Sampling should not stop if a swab at a given time is negative. We will also monitor duration of MV and ICU and hospital mortality. Patients will be followed up to 60 days after randomization. Data recorded on CRFs will be double-entered into an electronic database and validated by trial staff.

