### Outcome measures

The primary outcome is all-cause mortality at 60 days after randomization. Site investigators will be reporting patient status at 60 days, irrespective of whether the patient continued hospitalized in the same hospital, in another type of health care facility, or discharged home. If patients are discharged alive from hospital before day 60, the information on clinical status at 60 days will be obtained from the electronic clinical record. The Public Health Care System in Spain provides information about the clinical status of any patient through the electronic clinical record system that exists in any public hospital, city, province, or region. In the few cases in which no information could be not obtained from the electronic clinical record (e.g., the patient is not in contact with the outpatient clinic or home care professionals), the local investigator will contact the patient or relatives by phone to ensure the status of the patient at day 60 after randomization. In addition, lead investigators in each site will confirm the recorded 60-day mortality at the time of data analysis.

The secondary outcome is the number of VFDs at 28 days, defined as the number of days alive and free of MV from the day of randomization (day 1) to day 28 after enrollment, on which a patient breathe without assistance. For a day to be considered a ventilator-free day, the patient must breathe without assistance for the full 24 h, i.e., for every breath during that day. The following considerations will be taken into account when calculating the number of VFDs: (i) successful liberation from MV should last more than 48 h without reintubation in patients who survive 28 days after randomization; (ii) extubation only count from the last successful extubation within a 28-day survivor; and (iii) VFDs are awarded zero days if the patient is ventilated for 28 days or more, or die before 28 days (irrespective of intubation status) [20]. Other clinical outcomes include mortality in the ICU, mortality at day 28, duration of MV, length of stay in the hospital for survivors, and the time (in days) from treatment initiation to death. Virologic measures will include the proportions with viral RNA detection over time. Safety outcomes in both groups will include adverse events that occurred during treatment (hyperglycemia, new infections), serious adverse events, and premature discontinuation of treatment.

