### Reporting adverse events

According to Spanish legislation, adverse events should be reported to the Trial Coordinator and to the referral Ethics Committee for review. All adverse events occurring during the study observed by the investigator will be recorded on the data forms. An adverse event is defined as any untoward medical occurrences in a patient during the trial that are not considered related to the clinical state of the patient. Serious adverse events related to the protocol will be sent to the DSMB within 24 h after being received by the trial coordinator. Expected adverse events or complications related to the protocol would include occurrence of hyperglycemia (blood glucose > 180 mg/dL) and new infections (e.g., pneumonia or sepsis) after randomization. All unexpected, and related or possibly related, adverse events will be reported to the institutional review board. Adverse events considered related to the trial, as judged by the investigators, will be followed until resolution or until the event is considered stable. Related adverse events that result in a participant’s withdrawal from the study or are present at the end of the study will be followed up until a satisfactory resolution occurs. The investigator would seek information on adverse events by specific questioning and examination.

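### The safety outcome has two conflicting time windows, one undefined for controls, and an adverse event definition that rests on open-label attribution

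*Protocol article*

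**What the plan says.** Outcome measures sets the safety comparison: "Safety outcomes in both groups will include adverse events that occurred during treatment (hyperglycemia, new infections), serious adverse events, and premature discontinuation of treatment". The on-treatment limit is attached to hyperglycemia and new infections. Serious adverse events are a separate item without a stated window.

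The length of treatment is in Dexamethasone therapy and general procedures: "Treatment with dexamethasone will be given for a maximum of 10 days after randomization, independently of the intubation status". Under Randomization and masking, controls receive standard intensive care alone, without placebo. The Discussion names the lack of blinding as a major limitation.

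Reporting adverse events defines an adverse event as "any untoward medical occurrences in a patient during the trial that are not considered related to the clinical state of the patient". It has adverse events recorded throughout the study. It names hyperglycemia (blood glucose > 180 mg/dL) and new infections such as pneumonia or sepsis as expected events after randomization, with no end at day 10.

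Clinical and laboratory monitoring adds, for patients in either arm: "We will record complications, such as other infections, barotrauma, and sepsis". Follow-up runs to 60 days.

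**The concern.** Hyperglycemia and new infection are the harms that the article itself names as expected. Comparing them between arms needs one time window that means the same in each arm, and a rule for what counts that does not depend on knowing the arm. As written, neither is secured.

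- **Window.** Two sections give different periods for the same events. One of these periods is tied to a treatment that half the patients do not receive.
- **Counting rule.** Pneumonia is part of the entry criteria (Study population). Whether a later pneumonia or sepsis belongs to the patient's clinical state is therefore a real judgement, made at the bedside where the arm is known. A control infection may be put down to the illness and the same infection on dexamethasone to the drug, or the reverse.

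At stake is the credibility of the safety table, not the mortality result.

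**Working it through.** **Step 1. The sections side by side**

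| Item | Outcome measures | Reporting adverse events | Clinical and laboratory monitoring |
|---|---|---|---|
| Hyperglycemia, new infections | On treatment, both groups | After randomization | Other infections and sepsis recorded as complications, both arms |
| Window on dexamethasone | Ends by day 10 at the latest | No end stated; recording during the study | Follow-up to day 60 |
| Window for controls | None can be derived | As above | As above |
| Serious adverse events | No window stated | Protocol-related ones go to the DSMB within 24 h | Not addressed |
| Filter on what counts | None stated | Not attributed to the clinical state | None stated |

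The same sentence in Outcome measures also lists "premature discontinuation of treatment" for both groups. Controls have no study treatment to discontinue. This supports the reading that the sentence was written with the dexamethasone arm in mind.

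**Step 2. What a day-10 limit leaves out**

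The documents give no infection rate. *Assumption:* a constant daily hazard h of first new infection between 0.5% and 3%, the same in both arms. Ignoring death and discharge, the risk by day d is F(d) = 1 − exp(−h·d), and the share of day-28 infections falling after day 10 is 1 − F(10)/F(28).

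| h per day | F(10) | F(28) | F(10)/F(28) | Share after day 10 |
|---|---|---|---|---|
| 0.5% | 4.9% | 13.1% | 0.37 | 63% |
| 1% | 9.5% | 24.4% | 0.39 | 61% |
| 2% | 18.1% | 42.9% | 0.42 | 58% |
| 3% | 25.9% | 56.8% | 0.46 | 54% |

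Death competes with infection, so I repeated this with the article's own control mortality of 55% by day 60, taken as a constant hazard: c = −ln(0.45)/60 = 0.0133 per day. Then F(d) = h/(h + c) × [1 − exp(−(h + c)·d)]. The share after day 10 falls to 58% at h = 0.5% (F(10) = 4.6%, F(28) = 11.0%) and to 50% at h = 3% (24.4% and 48.7%). Discharge, or a hazard that falls with time, would lower it further.

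**Step 3. What unequal windows would do, if sites or analysts used them**

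If dexamethasone patients were counted for 10 days and controls for 28, the apparent risk ratio with no true difference would be F(10)/F(28), that is 0.37 to 0.46 in the table above. With a common window it is 1.0. The article does not prescribe unequal windows; this is the cost of leaving the control window open.

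**Step 4. What unequal attribution would do**

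*Assumption:* the true infection risk p is equal in both arms, with 90% of infections in one arm and 60% in the other classed as adverse events. The observed difference is p × (0.90 − 0.60).

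- p = 20%: 18% against 12%, 6 points
- p = 40%: 36% against 24%, 12 points

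The risk ratio is 0.90/0.60 = 1.5, or 0.67 if the attribution runs the other way. These shares are illustrative. They show that the bias could be large and that its sign cannot be known in advance.

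**The case against.** The strongest reply is that the data are not lost. Adverse events are recorded throughout the study, new infections are named from randomization on, complications are recorded on one standardized form for both arms, and a late serious infection can enter as a serious adverse event. All of this stands. A reader might infer that infections after day 10 are missed altogether. The documents do not support that: what falls outside is the non-serious late infection, and only from the outcome as stated in Outcome measures.

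Second, a reader might infer that the arms are necessarily measured differently. That is not stated either. The sentence says both groups, and a common 10-day window from randomization is a compatible reading that would give a narrower but fair comparison. The article does not say that this is the window, and it conflicts with the wording under Reporting adverse events. The full protocol may settle it, but the conflict is in the published text itself.

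Third, the adverse event definition names no assessor. The phrase about investigators' judgement in that section concerns relation to the trial. Hyperglycemia has a numerical threshold, and new infections are listed by name as expected events. This limits the scope for judgement, mainly for hyperglycemia. It does not remove it for infections, and an analyst unaware of group assignment cannot restore events already classed as part of the illness.

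Fourth, a reader might infer that the DSMB's reports pass through the same filter. They do not. The rule is: "Serious adverse events related to the protocol will be sent to the DSMB within 24 h after being received by the trial coordinator". That filter is relation to the protocol, not to the clinical state, and nothing says it is the DSMB's only source of information.

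**Conclusion.** The point holds as a conflict in the stated rules. The two sections give different windows for the same events, the on-treatment window cannot be applied to controls, and the adverse event definition leaves the infection count open to attribution that may differ by arm. Correcting it is worthwhile but does not bear on the validity of the primary analysis, since all-cause mortality at 60 days is unaffected.

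The size cannot be taken from the documents. Under the assumed hazards, a day-10 limit would leave out about half to three fifths of first infections by day 28 (50% to 63%, with or without allowance for death). The window and attribution distortions in steps 3 and 4 are illustrations of what could happen, not estimates for this trial. The conclusion rests on the wording, not on these figures.

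**What to change.** For the between-arm safety comparison, reconcile the two sections as follows:

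1. State one window that starts at randomization and has the same rule in both arms, for example to day 28, death or ICU discharge, whichever is first. If death or ICU discharge can close the window, report days at risk by arm, since these may differ.
2. Count hyperglycemia by the stated threshold of > 180 mg/dL, and new infections from the complications already recorded on the case report form, by the same criteria in both arms and whatever the presumed cause.
3. State the window for serious adverse events as well.
4. Keep judgements of relatedness for expedited and regulatory reporting only.
5. Report premature discontinuation of treatment for the dexamethasone arm only.

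The cost is a change of wording and one common window on the form. Raw event counts will be higher, because events attributed to the illness are now included, and there will be somewhat more recording after day 10. Sample size and the primary analysis do not change.

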### Sample size calculations

The trial was designed to be initiated in rapid response to the COVID-19 public health emergency. We estimated the sample size on the assumption that treatment with dexamethasone could reduce all-cause 60-day mortality by 20%. Our baseline reference was 50–55% based on recent observational studies from China [4]. Depending on the estimated 60-day mortality, we studied various group-size scenarios with cohorts of 93 to 100 patients in each arm to detect a 20% difference with a power of 80%, at a two-sided significance level of alpha = 0.05. The R function power.prop.test was used to estimate the sample size requirement which is based on a *z* test. A population size of 192 patients (96 in each arm) will provide 80% power to detect a 20% absolute reduction, from 55% on the control group to 35% in the experimental group. To account for up to 5% potential losses to follow-up, we will randomize 200 patients. We will only analyze patients that are enrolled and randomized to receive treatment. There will not be a formal interim analysis. However, after recruitment of 70% of the patients, an independent statistician will perform a conditional power analysis. If the conditional power at that time is ≥ 70% but < 80%, the external Data and Safety Monitoring Board (DSMB) can recommend an increase in sample size to achieve 80% power. The conditional power analysis will be performed at the Applied Health Research Center, Li Ka Shing Knowledge Institute of St. Michael’s Hospital, Toronto, Canada. Since the conditional power analysis will not be used to stop the trial early due to a treatment difference, no adjustment to alpha is required. The DSMB could decide to stop the trial at any point for safety reasons. Also, in a context of a pandemic, it is plausible to discontinue the trial if no new patients are enrolled during a prolonged period of time. The decisions of the DSMB will be communicated to the principal investigators in a letter (sent by email). If the DSMB reaches a decision that the trial must be terminated early for safety reasons, they will email and call either one of the PIs within 24 h of making this decision.

### Statistical analysis

Data will be collected in each participating ICU using a standardized form. Then, the data will be transmitted to the coordinating center whenever a patient dies or is discharged from the hospital. Before entering the data into a computerized database at the randomization center, a trained data collector will check the completeness and the quality of information. Logical checks will be performed for missing data and to find inconsistencies, especially regarding clinical diagnosis, date, and severity scores. If necessary, the data collector will contact the investigator by phone to validate the data or reformat the data for entry into the database. Automatic range and completeness checks are performed as data are entered into the database. All analyses will be done according to the intention-to-treat principle without adjustment for multiple comparisons for the secondary outcomes since these are considered exploratory in nature. Baseline characteristics will be summarized descriptively, as appropriate (i.e., means (SD) or median and quartiles for continuous variables and counts/percentages for categorical/binary variables). Primary and secondary outcomes will be reported as observed between-group differences with 95% confidence intervals (CI) and two-sided *p* values. The 60-day mortality will be compared using a chi-squared test, and the treatment effect will be expressed as a risk difference with 95% CI. The risk ratio and 95% confidence interval will also be computed. It is expected that the primary outcome will be ascertainable for everyone. Nevertheless, should missing outcomes be a problem, an inverse probability weighted analysis will be conducted. VFDs will be assessed with the Mann-Whitney *U* rank test. Since the nonparametric test works with ranks, it is usually not possible to get a CI with exactly 95% confidence. Thus, the 95% CI for the difference between medians for VFDs in both groups will be estimated using a bootstrap procedure (10,000 replications).

Other continuous outcome variables will be compared with the Student’s *t* test. The treatment effect will be expressed as mean differences with 95% confidence intervals. For variables where there are major concerns about the underlying assumptions for the *t* test, the Mann-Whitney *U* rank test will also be used for a sensitivity analysis. Other categorical outcome variables will be compared using a chi-square test or Fisher’s exact test if expected counts are < 5. The treatment effect will be expressed as a risk difference with 95% confidence interval as well as the risk ratio. The time to hospital discharge will be summarized with cumulative incidence curves, treating death as a competing risk and compared using a cause-specific Cox model, and the treatment effect will be expressed as a hazard ratio with 95% confidence interval. Two-sided testing will be used for all inferential comparisons. A *p* value of less than 0.05 will be considered to indicate statistical significance for the primary outcome. Given the controversies around significance testing, *p* values will always be accompanied by point estimates of treatment effect and 95% confidence intervals. Analyses will be done by an independent statistician who will be unaware of group assignment.

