### Enrollment into the study

Onset of ARDS is defined as the day and time when the patient first met moderate-to-severe ARDS criteria [14]. An enrichment strategy to decrease heterogeneity and to restrict enrollment to screened patients at higher risk of death, thereby allowing the use of mortality as a primary outcome, is used as follows. We will identify patients with established moderate-to-severe ARDS by a two-step process: (i) mandatory standardization of measurements of PaO_2_/FiO_2_ at 12 ± 3 h after the ARDS diagnosis using a standardized ventilatory setting [8, 15], on PEEP of ≥ 10 cmH_2_O and FiO_2_ of ≥ 0.5 because the cutoff value of PaO_2_/FiO_2_ is an important determinant for ARDS stratification, and oxygenation in COVID-19 pneumonia/ARDS improves in many patients after initial inclusion criteria with low-tidal volume MV, moderate to high levels of PEEP, and prone positioning [10]; (ii) only patients with a PaO_2_/FiO_2_ of ≤ 200 mmHg under these ventilatory settings are eligible for randomization.

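### The unadjusted primary mortality test is valid, but prespecifying adjustment for baseline severity already collected would be a cheap gain in precision

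*Protocol article*

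**What the plan says.** Under Statistical analysis, the protocol article names the test and effect measure for the primary outcome: "The 60-day mortality will be compared using a chi-squared test, and the treatment effect will be expressed as a risk difference with 95% CI". A risk ratio is added. The estimates are crude by design: "Primary and secondary outcomes will be reported as observed between-group differences with 95% confidence intervals (CI) and two-sided" p values. Baseline data have a descriptive role only: "Baseline characteristics will be summarized descriptively, as appropriate". The one other method named for the primary outcome is inverse probability weighting, and that is for missing outcomes.

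The sample size rests on the same unadjusted comparison: "The R function power.prop.test was used to estimate the sample size requirement", and "A population size of 192 patients (96 in each arm) will provide 80% power to detect a 20% absolute reduction, from 55% on the control" arm to 35% in the dexamethasone arm.

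The trial nevertheless collects severity data before randomisation:
- Clinical and laboratory monitoring lists the "Acute Physiology and Chronic Health Evaluation II (APACHE II) score [18] on days 0 and 1", and SOFA on day 0 and later days. Day 0 is the day of ARDS diagnosis.
- Enrollment into the study requires "mandatory standardization of measurements of PaO_2_/FiO_2_ at 12 ± 3 h after the ARDS diagnosis", taken under standard ventilator settings before a patient can be randomised.
- Age is needed for the eligibility check.

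**The concern.** Where baseline variables predict death, a standardised adjusted risk difference estimates the same quantity as the crude one with a smaller variance. The protocol itself treats oxygenation-defined severity as prognostic, because it uses the 12 h PaO2/FiO2 to select patients at higher risk of death. It then leaves that measurement and the day-0 scores out of the mortality comparison.

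Precision is at stake. The design has little spare power: 80% at 96 per arm for a 20-point effect. The Discussion puts the minimal important difference near 5 points and expects a smaller effect to be passed to meta-analyses, where a narrower interval is worth having.

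The choice of primary test is written down explicitly, so this comments on what the article fixes and not on detail left to an analysis plan.

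**Working it through.** **Inputs from the protocol article.** Control risk 55%, dexamethasone risk 35%, 96 per arm, two-sided alpha 0.05, 80% power, 1:1 allocation, 200 randomised (Sample size calculations; Randomization and masking). **Assumed:** the prognostic strength of the baseline data, which the article does not give.

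**Step 1. Reproduce the plan's figure.** Pooled normal formula without continuity correction, as in power.prop.test:

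n = [1.96·√(2·0.45·0.55) + 0.8416·√(0.55·0.45 + 0.35·0.65)]² / 0.20²
= [1.96·0.7036 + 0.8416·0.6892]² / 0.04 = 1.959² / 0.04 = 95.9, so 96 per arm and 192 in total.

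Power at 96 per arm is 80.02%. It is 81.6% at 100 per arm (all 200 with an outcome) and 79.6% at 95 per arm. The plan's figure reproduces.

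**Step 2. Effect of a given variance reduction v.** Power is recomputed at effective size 96/(1 − v). The 95% CI half-width is 1.96·√[(0.2475 + 0.2275)/96·(1 − v)]. N for 80% power is 2 × (96·(1 − v) rounded up).

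| v | Power | CI half-width (points) | N for 80% |
|---|---|---|---|
| 0 | 80.0% | 13.8 | 192 |
| 5% | 82.0% | 13.4 | 184 |
| 10% | 84.0% | 13.1 | 174 |
| 15% | 86.1% | 12.7 | 164 |
| 20% | 88.1% | 12.3 | 154 |
| 25% | 90.0% | 11.9 | 144 |

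**Step 3. Link v to prognostic strength by simulation.** 6,000 trials per row, 96 per arm, one standard-normal baseline score, logistic model, standardised risk difference with influence-function SE, against the uncorrected chi-squared test. AUC is that of the score for death in the control arm.

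| AUC (assumed) | Chi-squared power | Adjusted power | Variance reduction |
|---|---|---|---|
| 0.50 | 81.5% | 81.7% | none |
| 0.61 | 79.8% | 81.7% | 3% |
| 0.66 | 80.4% | 83.8% | 8% |
| 0.70 | 79.2% | 85.0% | 12% |
| 0.74 | 81.0% | 87.5% | 15% |
| 0.79 | 79.6% | 89.5% | 24% |

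The Monte Carlo SE of each power is about √(0.8·0.2/6000) = 0.5 points, so compare within rows. The mean crude and adjusted estimates agreed to within 0.1 points in every row, so the estimand is unchanged. With no true effect (AUC 0.70, 55% in both arms), type I error was 5.5% for chi-squared and 5.3% adjusted.

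**Step 4. Three covariates, as the fix would use.**
- 10,000 null trials gave type I error of 5.5–5.8% adjusted against 4.8–5.4% unadjusted, a gap of 0.3 to 0.7 points.
- A separate run of 4,000 trials per setting gave 5.1–5.8% against 4.6–5.4% (Monte Carlo SE √(0.05·0.95/4000) = 0.34 points). A small-sample degrees-of-freedom correction brought the adjusted rate to 4.8–5.6% and kept nearly all of the power gain.
- Power gains across settings were again about 0 to 10 points. With logit slope 0.4, power rose from 80.2% to 82.6%.

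**Step 5. Small effects.** For 55% v 50% at 96 per arm: (0.05·√96 − 1.96·√(2·0.525·0.475)) / √(0.2475 + 0.25) = (0.490 − 1.384)/0.705 = −1.27, which is 10.2% power. A 23% variance reduction raises it only to 12.1%.

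**The case against.** The case for leaving the plan alone is substantial. The chi-squared test is valid under 1:1 randomisation, matches the sizing method and the stated effect measure, and suits a rapid-response trial that counts simplicity among its strengths. All of that stands, and it is why this is an efficiency suggestion and not a defect.

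A reader might infer more than the documents support:
- **That the covariates are strongly prognostic.** No AUC, coefficient or R² is given. The enrichment step also narrows the PaO2/FiO2 range, which may put the gain near the lower end. Age and the day-0 scores are not restricted in the same way.
- **That chance imbalance would bias the result.** Imbalance in one score alone could move the crude risk difference by ±3.8 points (AUC about 0.66) to ±6.8 points (AUC about 0.79) over its 95% range. Under randomisation that variation is already contained in the unadjusted interval and p value. Adjustment removes some of it and does not correct an invalid analysis.
- **That randomisation is unstratified.** The article names permuted blocks and no stratification factor, but it condenses a fuller document that may name one.
- **That adjustment would let the trial address small effects.** Step 5 shows that it would not, and the Discussion says the trial is aimed at large signals.

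One technical objection changes the fix. An uncorrected SE with three covariates is mildly anti-conservative at this sample size, so part of the apparent gain would be spurious. A small-sample correction deals with this at little cost in power.

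**Conclusion.** The point holds as a cheap improvement and not as an error. The planned analysis is valid and achieves its stated 80% power under its own assumptions. A prespecified standardised risk difference would target the same quantity and, at 96 per arm with 55% v 35%, add about 0 to 10 points of power by removing 0 to about 25% of the variance.

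That range assumes a combined baseline score with AUC between 0.50 and about 0.79. In the simulation a useless score cost nothing material. The direction is secure whenever the covariates are prognostic. The size is not known from the documents.

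**What to change.** Prespecify as the primary analysis a standardised (marginal) risk difference from a logistic model with treatment, age, the 12 h standardised PaO2/FiO2 and one day-0 severity score, either SOFA or APACHE II, chosen in advance.

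- **Covariate timing.** Use only pre-randomisation values. Day 1 is the day of randomisation and the first dose follows at once, so day-1 scores may already reflect treatment.
- **Inference.** Take the 95% CI and p value from a robust or influence-function SE with a small-sample degrees-of-freedom correction, or from a bootstrap.
- **Supporting analysis.** Keep the chi-squared test and crude risk difference.
- **Deadline.** The trial is open-label, so settle this before any comparison of outcomes by arm, including the conditional power analysis at 70% recruitment (0.70 × 200 = 140 patients).

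The cost is a change of wording and slightly more complex reporting. If the SE is left uncorrected, there is also a type I error up to about 0.5 to 0.7 points above that of the unadjusted test. No new data collection is needed.
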